Ideally, we would like to know the drug level just prior to a detectable parasitemia in the participant since at that level, parasites were able to begin to replicate. Since it is impossible to anticipate when a new patent parasitemia will occur, we will attempt to predict the level retrospectively by obtaining the pharmacokinetic curve in the population. We will also measure the level at the time of recurrent parasitemia in case the participant was found to vary significantly from the mean.

1. Assess the effect of population movements on the risk of malaria infection.

- Risk of malaria in children who traveled outside the city compared to those who did not.

Our interest is the first incident of malaria. Malaria illness will be defined as any level of microscopy-confirmed *Plasmodium falciparum* parasitemia accompanied by signs or symptoms consistent with malaria either leading to treatment-seeking behavior or reported during follow-up visits. This definition is more inclusive since practicing physicians in a malaria endemic area would treat a person who presents complaining of illness and who had documented parasitemia. This definition will enable the longitudinal study to capture all first episodes of malaria illness that would be treated under standard medical practice. Time to malaria illness after baseline is defined as number ofdays without malaria illness after baseline up to the date of the first illness. Dates will be recordedfor all the events occurring prior to or during follow-up.

1. Assess the spatial patterns and the environmental determinants of malaria infection

- Distribution of malaria cases in relation to environmental factors in Ndirande.

In order to evaluate whether there is clustering of cases and/or spatial correlation with environmental variables, we will carefully analyze the spatio-temporal pattern of all cases. All new malaria illnesses after the initial treatment will be escorted home and their location geo-referenced using GPS. Information will be entered into ArcGIS (*ESRI, Redland, CA*) to create a spatial point pattern. This will be linked to the database with information on health, demographic, economic, social, ecological and agricultural characteristics.

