# Study Design

## Study site

Ndirande is a peri-urban hillside township adjacent to Blantyre, the largest city in Malawi. Accurate census data are not available for Ndirande, but the population is approximately 200,000. Malaria transmission is year-round, with a seasonal peak from December to March corresponding to the rainy season. The Ndirande Health Centre is the sole government health facility serving the entire township, and consists of a complex of buildings with outpatient clinics and a maternity center. Our field team of clinicians, nurses and technicians has been conducting malaria drug efficacy studies at the Health Centre continuously since 1997 and has an excellent relationship with the community. During this time more than 3,000 participants have been enrolled in five studies, including clinical trials and longitudinal studies. After operating in dedicated space within the Centre facility for several years, in 2002 we established a new research facility on the Centre grounds. The Blantyre Malaria Project Research Clinic contains rooms for clinicians and nurses, laboratory space for the microscopists, a dispensary, an administrative office, a conference room and a computer room for real time data entry. We maintain a close relationship with the Ndirande Health Centre government workers. When we provide diagnosis and treatment in the context of our clinical studies, we offer relief from overcrowded conditions in the Centre. Back-up clinical and laboratory support is available a 10 minutes drive from the Centre at the pediatric research ward in Queen Elizabeth Central Hospital.

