# Study Enrollment and Withdrawal

The study population will be drawn from children who are brought to the Ndirande Health Centre and are found to have uncomplicated malaria. Six hundred forty children will be enrolled. We expect enrollment to occur over an 18-month period so the entire study duration will be two to two and a half years, but the duration for each participant will be one year.

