## Enrollment/Baseline

After informed consent is obtained, a case record form including demographic information, previous medication exposure, allergy history and physical examination will be completed. The clinician will ask the parents/guardians about their plans to remain in the area and their willingness to bring the child for all scheduled and unscheduled follow-up. If the participant remains eligible, a study number will be assigned. The participant will be sent to the laboratory for venipuncture to obtain a complete blood count, ALT, creatinine, chloroquine level CBC and parasites for cryopreservation. Two attempts will be made to obtain these specimens. If the technicians are unable to obtain a sufficient specimen, the finger will be pricked to obtain 0.5 mL for a complete blood count, ALT and creatinine. All enrolled children will be escorted home where the location of the household will be recorded using GPS. At home, a questionnaire on socioeconomic status based on household assets will be administered and detailed directions of their home recorded to facilitate active follow-up.

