## Final Analysis Plan

The final analysis of the primary objective will be a comparison of incidence rates of malaria treatment episodes per year of follow-up (not including the first infection occurring at enrollment) in each arm of the study. The rates and 95% confidence intervals will be calculated using Poisson distribution. Reported antimalarial drug use without documented positive malaria smear will not count as a malaria treatment episode. Malaria episodes treated with non-study medicines at Queen Elizabeth Central Hospital with verified positive malaria smears will be counted as malaria treatment episodes, and any such treatments will be compared among groups to rule out bias due to different rates of non-study treatment. Withdrawal of participation is described above and includes participants who miss ≥ 2 consecutive routine follow-up visits. For the primary study endpoint, follow-up time for participants while they are enrolled in the study will be included in the analysis. For participants who were withdrawn after missing > 2 consecutive follow-up visits, time after the last visit will be censored from incidence analysis.

Drug efficacy for the first and subsequent episodes of malaria will be compared using Kaplan-Meier 28-day survival estimated and compared using Cox proportional hazards regression. Per-protocol analysis will be used to compare treatment efficacy, with data excluded from treatment episodes for which treatment outcome cannot be determined. Survival analysis will also be used to assess time to first resistant infection in each arm. Categorical data including episodes of liver, kidney or neurological toxicity and presence of anemia will be compared using 2 analysis. Logistic regression will be used to adjust for covariates.

Survival analysis will be used to assess the role of travel outside of Blantyre and bed net use on the risk for malarial and time to first malaria episode. This analysis will be conducted both with and without the inclusion of treatment arm as a covariate in the analysis.

Data will be entered in to the database on the computers at the field site. On a daily basis, the data will be transferred via the internet to the EMMES corporation web-based system.

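### Section 11.3 names only treatment arm as a covariate for the non-randomised travel and bed-net analyses, so confounding by season, age or household wealth could bias both estimates in either direction

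*Protocol*

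**What the plan says.** The protocol's Final Analysis Plan (11.3) states: "Survival analysis will be used to assess the role of travel outside of Blantyre and bed net use on the risk for malarial", and adds time to first episode as an outcome. It then says: "This analysis will be conducted both with and without the inclusion of treatment arm as a covariate in the analysis". No other covariate is named for these models. The only other adjustment sentence in 11.3, "Logistic regression will be used to adjust for covariates", follows the categorical toxicity and anemia outcomes and lists no variables.

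The travel outcome for Objective 7, in Secondary Outcome Measures (3.2.2), is: "Risk of malaria in children who traveled outside the city compared to those who did not". The same section counts time to malaria in days from baseline. Bed-net use is not part of Objective 7 and enters the analysis only through 11.3.

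Other sections bear on confounding:

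- Study site (4.1): "Malaria transmission is year-round, with a seasonal peak from December to March corresponding to the rainy season".
- Study Enrollment and Withdrawal (section 5): "We expect enrollment to occur over an 18-month period".
- Enrollment/Baseline (7.2): demographic information goes on the case record form, and "a questionnaire on socioeconomic status based on household assets will be administered".
- Follow-up (7.3): recent travel and bed-net use are asked at each four-weekly routine visit.
- Secondary Outcome Measures (3.2.2): event dates are recorded.

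**The concern.** Children who travel, or who sleep under a net, are not a random subset. Comparing them with the others requires adjustment for whatever drives both the exposure and malaria. Season is a documented driver of malaria here and may well influence travel. Age and household wealth plausibly influence net use, travel and malaria. All of these are, or can be derived from, data the trial already collects.

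Treatment arm is a different kind of variable. Being randomised, it should be close to unrelated to how families travel or use nets, so including or omitting it leaves confounding by season, age or wealth almost untouched.

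Two consequences follow if 11.3 is carried out as worded. The travel estimate for Objective 7 and the separate bed-net estimate may be biased. The two planned versions would also tend to agree, and a reader could take that agreement as a sign of robustness when both carry the same bias.

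**Working it through.** The protocol gives no figure for these analyses, so there is nothing to reproduce. The check asks what season alone could do, and whether adjusting for arm would remove it.

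**Inputs from the protocol.** The peak runs from December to March, which is 4 of 12 months (4.1). Accrual takes 18 months (section 5) and time runs from baseline (3.2.2), so a given day of follow-up falls in different calendar months for different children. The time scale therefore does not absorb season. There are 640 children, each followed for one year.

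**Assumed inputs, because the protocol does not give them.** These are the ratio r of the peak to the off-peak malaria rate, the share s of travel time that falls in the peak, and monthly travel prevalence. The true travel effect is set to none.

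**Step 1: rate during travel against the year-round average.** With travel treated as time-varying:

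spurious ratio = (s·r + 1 − s) / (r/3 + 2/3)

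For r = 3 the denominator is 1 + 0.667 = 1.667. The numerators are:

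- s = 0.2: 0.6 + 0.8 = 1.4, giving 0.84
- s = 1/3 (even spread): 1 + 0.667 = 1.667, giving 1.00
- s = 0.5: 1.5 + 0.5 = 2.0, giving 1.20
- s = 0.7: 2.1 + 0.3 = 2.4, giving 1.44

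The same formula across a range of peak heights:

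| Assumed r | s = 0.2 | s = 1/3 | s = 0.5 | s = 0.7 |
|---|---|---|---|---|
| 2 | 0.90 | 1.00 | 1.125 | 1.275 |
| 3 | 0.84 | 1.00 | 1.20 | 1.44 |
| 4 | 0.80 | 1.00 | 1.25 | 1.55 |

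**Step 2: travel time against non-travel time.** Let a and b be the monthly travel prevalence in and out of the peak. The mean relative rate during travel is (a·r/3 + 2b/3) / (a/3 + 2b/3). For non-travel time, replace a and b by 1 − a and 1 − b. With r = 3, a = 20% and b = 5%:

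- travel: (0.200 + 0.033) / (0.067 + 0.033) = 2.333
- non-travel: (0.800 + 0.633) / (0.267 + 0.633) = 1.593
- ratio: 2.333 / 1.593 = 1.47

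With the prevalences reversed (5% in the peak, 20% outside) the ratio is 1.222 / 1.745 = 0.70. For r from 1.5 to 4 the range is 1.16 to 1.59 in the first pattern and 0.89 to 0.63 in the second. It is 1.00 when prevalence is equal.

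**Step 3: does arm help?** Time to first malaria was simulated for 640 children with 18-month accrual and 12 months of follow-up. The assumptions were a mean rate of 1.25 per year, r = 3 and no effect of travel or arm, with 150 replicates. A discrete-time proportional hazards model on time since baseline gave these average travel hazard ratios:

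| Monthly travel, peak / off-peak | No covariate | With arm | With season |
|---|---|---|---|
| 20% / 5% | 1.48 | 1.48 | 1.02 |
| 10% / 10% | 1.00 | 1.00 | 0.99 |
| 5% / 20% | 0.70 | 0.70 | 0.99 |

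The two versions named in 11.3 give the same biased answer, and a season term removes the bias.

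**Step 4: the fixed contrast.** If each child is classed once as traveller or non-traveller, a full year of follow-up contains all four peak months for everyone. Season then confounds only if traveller status is related to enrollment month or to length of observation. The ratios above do not describe that contrast. Its seasonal bias would be smaller and is not quantified here. Nor is any figure available for confounding by age or wealth, or for bed nets.

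**The case against.** The strongest reply is that a protocol need not list covariates for a secondary, observational model. Section 11.3 does not say that arm is the only covariate and excludes nothing; the statistical analysis plan, which was not available, may name more. This stands in part. A reader might infer that season, age and wealth have been ruled out, and the text does not support that: they are simply not named. But 11.3 does more than stay silent. It specifies a pair of analyses for a non-randomised contrast, and that pair does not address a seasonal driver the protocol itself describes.

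A reader might also infer that travel will look harmful. The protocol does not say when families travel, and the sign reverses if travel falls mainly in the drier months.

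Nor should arm be called incapable of confounding. Travel and net use are recorded after randomisation in an open-label trial (5.4.2, 7.3), so arm could influence them. Arm is also expected to affect the outcome (1.5 versus 1.0 episodes per year in 11.2), and a hazard ratio can shift when such a variable is added even without confounding. The simulation gave arm no effect on malaria, so it does not measure that shift. Presenting results with and without arm is reasonable inside a four-arm trial; it just does not deal with season, age or wealth.

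Finally, the outcome in 3.2.2 reads as a child-level contrast, to which the ratios for time-varying travel do not apply. That is correct and limits the size claimed. The visit-level questions permit a time-varying model, but 11.3 does not specify one.

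**Conclusion.** The point holds as a minor one. For the travel and bed-net survival analyses, 11.3 names only a covariate that does little against confounding, while season, age and household assets are collected but not tied to these models. Either estimate may be biased in either direction, and the two planned versions would share that bias.

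With travel time-varying, no true effect and a three-fold peak, season alone gives a ratio between 0.84 (20% of travel in the peak) and 1.44 (70% in the peak), and 1.0 if travel is evenly spread. The peak height and the travel timing are assumptions, so this range shows what is possible and is not a forecast. A fixed traveller contrast would be affected less.

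The consequence is confined to Objective 7 and to the bed-net analysis in 11.3. The randomised primary comparison does not depend on it.

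**What to change.** In 11.3, state that travel and bed-net use will be modelled as time-varying exposures from the four-weekly visit data. Use calendar time as the underlying time scale, or include season as a time-varying term. Adjust for age and the household-asset score, and keep treatment arm as an optional additional term.

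The cost is a sentence or two in 11.3 and modest programming. Visit and event dates, demographic data, the asset questionnaire and the visit-level exposure questions are already in the protocol, so no new data collection is needed.

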### Spatial analysis

Digital base maps (topographic and features) of Ndirande will be purchased from the National spatial data center of the Malawi Geographical Information Council (MAGIC). The base maps will provide main features of the study area such as road networks (type and pattern of roads) and waterways (community water sources, rivers and drainages) as well as administrative boundaries. They will also be linked to the database containing field data. We will also use the base maps to order the satellite imagery.

Highest resolution satellite imagery will be required to map surface features of the study area. This will allow capturing of all potential breeding spaces as well as land use and land cover within the study. This will not only complement the information provided on field surveys, but also facilitate the understanding of spatial distribution of malaria risk in Ndirande. It will also provide information on environmental disturbance in the area not captured by the field surveys and base maps.

At the moment, the highest resolution available satellite imagery is the 1-metre panchromatic provided by IKONOS (*Spacing Inc*) satellite. This should provide means of extracting and distinguishing relevant geographic information covering the study areas such as road networks, houses and open grounds, waterways (rivers and streams), ponds and swamps. Ground truthing will be done to validate the satellite images. In addition, data on elevation, levels of drainage around Ndirande will be mapped and geo-referenced using GPS.

The satellite images will be processed in ERDAS (*ERDAS Imagine, Atlanta, USA*). The information extracted will then be linked to the base maps and databases in ArcGIS. Proximity of the location of houses to a river or a stream and other putative sources of malaria transmission will be identified using buffer layers which will be created along, pools of water, rivers and streams. The percentage of buffer area to the total area in a village will be used as a covariate representing proximity to rivers/streams.

Spatial Cluster analysis will be used to identify an unusually high occurrence of morbidity that is clustered in space and time. In order to identify disease clusters in smaller areas located near a potential high risk factor (putative source: ponds, rivers, water pools, streams, swamps), focused spatial cluster analysis will be carried out to assess the presence of a statistically significant grouping of cases. A number of methods exist to reveal clusters of high and low malaria rates observed during the study period. Here we propose use of Kulldorff’s SaTScan statistic**.** SaTScan uses a replication method to create a spatial scan statistic by imposing a circular window, which is then centered around each of several possible centroids positioned throughout the study region. For each centroid, the radius of the window varies continuously in size from zero to an upper limit, thus creating an infinite number of distinct geographical circles, each being a possible candidate for a cluster. In addition, a recent local indicator of spatial autocorrelation (LISA), Getis G*i, statistic, will be used to detect hotspots of malaria illnesses and relate them to putative sources of malaria transmission *.*Gi* measures spatial association by using distance under the assumption that the variable has a natural origin, and would supplement the Kulldorff’s SaTScan.

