## Sample Size Considerations

In a previous longitudinal study of malaria in this population, we found that the mean annual incidence of malaria was approximately 2.5 episodes per year (59) with a standard deviation of approximately 2. Chloroquine is presently highly effective in treating malaria and has a prolonged prophylactic effect, so we have estimated a mean rate of 1.5 malaria episodes per year with chloroquine alone. We derived the sample size required to detect a decrease in the mean to 1.0 episodes per year assuming a Poisson distribution and using a 2 sided test with alpha= .05/3=.0166. The test size was adjusted to accommodate the 3 treatment versus control comparisons. With the above requirements and for a 2 treatment contrast, 120 subjects with complete observation are required per treatment arm to have 90% power (PASS 2005). To account for migration and other causes of attrition, we will enroll an additional 33% (40 subjects) in each regimen. We will accrue 160 per arm for a total of 640 subjects.

Because of the currently estimated efficacy of chloroquine alone in Malawi (in excess of 95%), we are unlikely to determine differences in initial administration (day 28) efficacy between the treatment arms. Power is limited as all arms should have very few early failures. Rates of anemia (<8 mg/dl) at the end of one year should be available in ~120 subjects per arm. The 95% CI half-width for the difference in anemia rates, calculating the variance with a rate of .2, is approximately .10. Thus, the selected sample size should be informative about larger treatment arm differences in anemia rates.

To determine the population pharmacokinetic curve for chloroquine, we have designed a randomized unbalanced study. All participants will have chloroquine levels determined prior to drug administration, at day 14 and at one additional randomly assigned time point. The assignment will be weighted to increase measurement on day two. Planned Interim Analyses

The DSMB will decide when it would like to conduct the interim analysis. The data to be reviewed at this meeting will include safety and efficacy data.

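### Proximity to rivers and streams is fixed as one land percentage per undefined village, although each enrolled child's house is located by GPS (minor; secondary objective 8 only)

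*Protocol*

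**What the plan says.** Secondary objective 8 (Protocol, Section 3.1) concerns spatial patterns and environmental determinants of malaria infection. Four places bear on the exposure measure.

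- **Spatial analysis (under Section 11.3), house level.** "Proximity of the location of houses to a river or a stream and other putative sources of malaria transmission will be identified using buffer layers". The buffers are drawn around rivers, streams and pools of water.
- **Spatial analysis, the next sentence, village level.** "The percentage of buffer area to the total area in a village will be used as a covariate representing proximity to rivers/streams".
- **Section 7.2, Enrollment/Baseline.** "All enrolled children will be escorted home where the location of the household will be recorded using GPS". Section 3.2.2 adds for later episodes: "All new malaria illnesses after the initial treatment will be escorted home and their location geo-referenced using GPS".
- **Section 4.1, Study site.** "Ndirande is a peri-urban hillside township adjacent to Blantyre, the largest city in Malawi". No villages or other sub-areas are listed, counted or delimited.

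The same section also plans analyses that work from locations: near ponds, rivers and similar sources, "focused spatial cluster analysis will be carried out to assess the presence of a statistically significant grouping of cases", together with a SaTScan scan statistic and the Getis Gi* hotspot statistic. The protocol names no regression model, unit of analysis or handling of clustering for the proximity covariate.

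**The concern.** The two adjacent sentences use different units. The first places houses relative to water; the second reduces proximity to the share of a village's land that lies inside a buffer. Three things follow directly from the wording.

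1. The value is constant within a village, so a child living beside a stream and a child living far from it in the same village are scored alike.
2. The percentage describes land, not where the enrolled children live. A village with much buffered but uninhabited ground would score high.
3. The independent units for this covariate are villages, and the protocol does not say what or how many they are.

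At stake is how well this one covariate can speak to objective 8. Its association with malaria would be ecological: it compares areas, and need not reflect what happens to children in houses near water. Depending on the model chosen, the test could also be too liberal or weak.

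**Working it through.** The protocol gives no sample size, power or ICC for the spatial objective, so it has no figure of its own to reproduce. The calculations below only show how far the result depends on quantities it does not give.

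**Inputs from the protocol.** "Six hundred forty children will be enrolled" (Section 5). Section 11.2 has "estimated a mean rate of 1.5 malaria episodes per year with chloroquine alone" and 120 children per arm with complete observation, so 4 × 120 = 480.

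**Assumptions, not in the protocol.** Number of villages J, ICC, between-village coefficient of variation (CV) of the malaria rate, share of houses inside a buffer, and effect size.

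**(a) Child-level test that ignores clustering.** For a covariate constant within villages of equal size m = 640/J:

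- design effect DE = 1 + (m − 1) × ICC
- actual size of a nominal two-sided 5% test = 2 × [1 − Φ(1.96/√DE)]

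Example with J = 10 and ICC = 0.01: m = 64, DE = 1 + 63 × 0.01 = 1.63, 1.96/√1.63 = 1.535, size = 12.5%.

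| J | ICC 0 | ICC 0.005 | ICC 0.01 | ICC 0.05 |
|---|---|---|---|---|
| 4 | 5% | 14% | 22% | 51% |
| 10 | 5% | 9% | 13% | 34% |
| 40 | 5% | 6% | 7% | 14% |

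The inflation runs from none to tenfold, depending on two unknowns. It disappears if clustering is modelled.

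**(b) Village-level test.** The village log rate is regressed on the percentage with J − 2 degrees of freedom. In simulation this test keeps its size (about 4 to 6%). Its power depends on how the effect is expressed.

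*Effect per SD of the village percentage.* 640 children, mean 1.5 episodes, rate ratio 1.2 per SD. The range shown is for CV 0.2 to 0.1.

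| J | Power |
|---|---|
| 5 | 27–61% |
| 10 | 63–95% |
| 20 | 88–99% |

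*Effect per house.* 480 children, mean 1.25 episodes (midway between the 1.5 and 1.0 of Section 11.2), rate ratio 1.3 for a house inside versus outside the buffer, 30% of houses inside. The between-village share is the fraction of the variance in buffer membership that lies between villages. The range is again for CV 0.2 to 0.1.

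| J | Power, between-village share 0.2 | Power, between-village share 0.5 |
|---|---|---|
| 5 | 7–10% | 9–15% |
| 10 | 9–15% | 16–30% |
| 20 | 14–20% | 26–41% |
| 40 | 18–23% | 36–49% |

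**Why the two sets differ.** With a share of 0.2, the SD of the village percentage is √(0.2 × 0.3 × 0.7) = 0.205. A house rate ratio of 1.3 then becomes exp(ln 1.3 × 0.205) = exp(0.262 × 0.205) ≈ 1.055 per village SD. Conversely, 1.2 per village SD corresponds to a house rate ratio of exp(ln 1.2/0.205) ≈ 2.4. The first set thus assumes a large house-level effect and the second a moderate one. The protocol supports neither choice over the other.

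**The case against.** The strongest reply has four parts.

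- **No model is stated.** A false-positive problem needs a child-level test, clustering ignored and real between-village variation. The protocol states none of these, and model form is commonly left to a statistical analysis plan, which is not at hand. This stands. A reader might infer that child-level tests will be falsely positive, but the documents do not support that.
- **The number of villages is unknown.** A reader might also infer that a valid village-level test has almost no power. That rests on an assumed number of sub-areas, effect size, buffer prevalence and between-village share. Other equally unsupported choices give high power. This stands too.
- **Objective 8 does not hang on this covariate.** The point pattern of cases in Section 3.2.2 and the focused cluster, SaTScan and Getis Gi* analyses use locations and do not need the village percentage. It would therefore be wrong to say that the GPS data are discarded from the study. They are lost from this covariate only. The cluster methods, however, look for clusters and hotspots; they do not estimate how malaria incidence varies with a house's proximity to water, which is what the covariate is meant to represent.
- **An area measure can be legitimate.** The share of land near water may be a sensible contextual variable. This is a reason to allow it as a secondary covariate, not to let it stand for the proximity of houses.

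None of these answers the mismatch between the two adjacent sentences or the undefined unit.

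**Conclusion.** The point holds as a minor, free improvement confined to secondary objective 8. The protocol says that house proximity will be identified and it collects the coordinates to do so. It then fixes a covariate that is constant within an undefined village and measures land rather than houses. That part needs no assumption.

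The consequences are conditional. A child-level test that ignores clustering could exceed its nominal 5%; a village-level test could have low power for a moderate house-level effect. Neither can be sized from the protocol, and the figures above illustrate sensitivity rather than measure this plan's error. The primary comparison of malaria incidence between arms is not touched.

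**What to change.** In the Spatial analysis section, replace the sentence on the village percentage with:

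> *Proximity will be measured for each enrolled child's house from its GPS position, as distance to the nearest river, stream or pool or as location inside the buffer, and will enter a child-level model of malaria incidence that accounts for clustering by sub-area.*

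Choose distance or buffer membership before the analysis and define the sub-areas. The percentage of buffer area may be kept as a secondary contextual covariate once they are defined.

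The cost is a change of wording and one GIS computation. House positions and buffer layers are already planned, so no new data are needed.
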